### Model validity

To assess model validity, we will explore changes in the case-mix of covariates over time in relation to delivery mode. Both maternal and child characteristics will be explored. The maternal characteristics considered will be: age at childbirth, ethnicity, parity, smoking status, body mass index before pregnancy, area deprivation coding, long-term allergy-related health conditions (asthma, eczema, allergic rhinitis and conjunctivitis), pregnancy and labour complications (premature rupture of membranes, postpartum haemorrhage, manual placental removal/retained products of conception) and antibiotic prescribing during pregnancy. The characteristics of the child considered include: gestational age, sex, ethnicity, birth weight, breastfeeding status and antibiotic prescribing during the first 5 years.

### Estimates of sample size and statistical power

To obtain estimates of statistical power and to estimate the impact of misclassification on estimates of increase in risk with prophylactic antibiotics before CS, we simulated the study (1) based on our estimates using the THIN database regarding the number of children with linked maternal data and asthma diagnosis rates in each year group between birth and 5 years of age, in line with previously published figures,^31^ and (2) using HES data based on estimates of children with linked maternal data and rates of children newly hospitalised for asthma assuming a readmission rate during the follow-up period of 50% based on HES statistics.^25^

In each simulation, we created a dataset for the whole study, with 13 birth cohorts from 2006 to 2018, and follow-up included across the first 5 years of life (curtailed at the end of 2018) (table 2). Each birth was classified by mode of delivery, and for those delivered by CS, whether antibiotics were given before skin incision, generated randomly using a binomial random number generator using an underlying probability of exposure to preincision antibiotics during that year of birth.

**Table 2 T2:** The number of births, years of follow-up and expected events in each simulation

	THIN-CPRD database	HES database
CS births	206 615	2 070 500
Postclamping antibiotics	111 508	1 115 670
Preincision antibiotics	95 107	954 830
VD births	570 774	5 973 100
Total births	777 389	8 043 600
CS person years of follow-up	792 265	8 661 832
Postclamping antibiotics	501 401	5 524 890
Preincision antibiotics	290 864	3 136 942
VD person years of follow-up	2 215 405	25 339 526
Total person years of follow-up	3 007 670	34 001 358
New events in children born by CS	7173	15 333
Postclamping antibiotics	5324	10 454
Preincision antibiotics	1849	4880
New events in children born by VD	20 378	44 906
Total events	27 551	60 240
Average event rate per 1000 person years	9.2	1.8

CPRD, Clinical Practice Research Datalink; CS, caesarean section; HES, Hospital Episode Statistics; THIN, The Health Improvement Network; VD, vaginal delivery.

Outcome events were randomly simulated according to the year-age event rates using a binomial random number generator, with increased rates in all those delivered by CS, and increased further in those who received antibiotics before skin incision. A risk ratio of 1.2 was used for increased risk of asthma with CS^32^ and then further increases with risk ratios from RR=1.10 to RR=1.20 (increasing in steps of 0.02) for the increase with antibiotics before skin incision rather than after cord-clamping.

Simulations were repeated 1000 times, and statistical power estimated by noting the proportion of simulations for which the lower limit of the 95% CI for the variable indicating whether antibiotics were given before skin incision was greater than a risk ratio of 1. We also recorded the estimates of the relative risk to assess attenuation bias created by misclassification.

The model which we fitted to analyse the simulation data included a trend term for the probability of receiving preincisional antibiotics with values 2006–2009=0, 2010=0.2, 2011=0.4, 2012=0.6, 2013=0.8, 2014–2018=1 with a zero value for those delivery vaginally (in the final analysis, we will use probabilities for each year obtained from the survey).

For the primary care data, we have 80% power of detecting a 16% relative increase in risk of asthma and over 90% power of detecting an 18% relative increase in risk, and being able to estimate them with a maximum of 15% underestimation from misclassification. For the HES admission data, we have over 80% power to detect a 10% relative increase in risk of asthma and 90% power to detect a 12% relative increase in risk with similar rates of underestimation due to misclassification.

The study will also be adequately powered to detect differences in the other primary outcome of interest (eczema) as incidence of clinician-diagnosed eczema is higher than asthma incidence in children in the UK.^33–35^

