**Methods and analysis:**

A controlled interrupted time series study will use anonymised mother-baby linked routine electronic health records for children born during 2006–2018 recorded in UK primary care (The Health Improvement Network, THIN and Clinical Practice Research Datalink, CPRD) and secondary care (Hospital Episode Statistics, HES) databases. The primary outcomes of interest are asthma and eczema, two common allergy-related diseases in childhood. In-utero exposure to antibiotics immediately prior to CS will be compared with no exposure when given after cord clamping. The risk of outcomes in children delivered by CS will also be compared with a control cohort delivered vaginally to account for time effects. We will use all available data from THIN, CPRD and HES with estimated power of 80% and 90% to detect relative increase in risk of asthma of 16% and 18%, respectively at the 5% significance level.

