### Exclusion criteria

Children with missing delivery information will be excluded. In case of multiple births (eg, twins), one of the children will be randomly selected for inclusion to ensure independence of observations.

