### Data sources

To maximise the sample size, we will combine two UK-wide primary care research databases, THIN and CPRD, containing anonymised patient records of over 10% of the UK patient population.^19^ Both databases are broadly generalisable to the UK population in terms of demographics and medical condition prevalence.^20 21^ There is overlap between the databases at general practice level, with THIN and CPRD containing 37% and 46% unique practices, respectively. The databases do not use the same identifiers for patients or practices, but the overlapping practices can be identified reliably using patient registration, demographic and medical record information and the duplicates removed to create a combined THIN-CPRD dataset.^19 22^

Information on mothers and their children in the THIN-CPRD dataset can be linked using the family identification code, pregnancy codes, mother’s registered or estimated delivery date, child’s month of birth and gestational age at delivery. This is the optimal linkage method allowing identification of a large proportion of mother-child pairs.^23 24^ In addition, in both THIN and CPRD a large proportion of patients (about 30% and 60%, respectively) have linked hospital record data. Our estimates using THIN suggest that while the mode of delivery is accurately recorded in primary care (98% verified against hospital records), the recording is incomplete (the delivery mode is known for 55%–64% of children). The mode of delivery is well recorded in hospital records,^3^ therefore where linked hospital data are available, this will increase the sample of children with known mode of delivery where this is missing in primary care data.

To allow us to investigate more severe outcomes of interest requiring hospital admissions which are better recorded in secondary care, we will also create a mother-child linked database using anonymised Hospital Episode Statistics (HES) data collected for all NHS hospital admissions in England.^25^ This is a complex task requiring considerable expertise in record linkage, because in the UK there is no shared identifier to link maternal and child records in HES. It is, however, possible using deterministic and probabilistic linkage to attribute up to 98% of baby and mother secondary care records, as has been demonstrated in other large-scale studies of maternal and early life course research.^26 27^

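### The primary-care power calculation is described for all children linked to their mothers, with no stated allowance for the further rule that delivery mode be known

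*Protocol article*

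**What the plan says.** Under Eligibility criteria, a child enters if the mother's and child's records can be linked and if delivery by caesarean section (CS) or vaginally (VD) can be identified from primary care records, hospital records or both. Exclusion criteria repeats the second condition: "Children with missing delivery information will be excluded".

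Data sources reports, from the authors' THIN estimates, that mode is accurate where recorded but that "the recording is incomplete (the delivery mode is known for 55%–64% of children". It adds that about 30% of THIN and 60% of CPRD patients have linked hospital data, which will supply mode where the GP record lacks it.

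The section on sample size and power describes the primary-care simulation input as "based on our estimates using the THIN database regarding the number of children with linked maternal data and asthma diagnosis rates in each year group". It then says "Each birth was classified by mode of delivery", and Table 2 divides all 777 389 THIN-CPRD births into 206 615 CS and 570 774 VD. Neither the text nor the table mentions an allowance for unknown mode. The section concludes: "For the primary care data, we have 80% power of detecting a 16% relative increase in risk of asthma". At an 18% increase it claims power above 90%. The Abstract repeats 80% and 90% for these effects.

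**The concern.** Two conditions define the analysable child, and the planning population is described by only one of them. Delivery mode is not a covariate that could be missing and handled later. It separates the CS series from the VD control series, so a child without it cannot enter the model. The article's own figures also show that an appreciable share of primary-care children would lack it, even after hospital records are used.

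If the simulated cohort is the linked cohort before that loss, the quoted power belongs to a larger study than the one that can be run. The Aim section says the results will either support the current recommendation or prompt a weighing of risks, so the sensitivity quoted in the Abstract is the yardstick against which a null asthma result in primary care is likely to be read.

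**Working it through.** **The plan's own figure.** Table 2 adds up: 206 615 + 570 774 = 777 389 births, and 7173 + 20 378 = 27 551 events. The stated power cannot be rerun exactly, because the year-by-age event rates and the true exposure probabilities used in the 1000 simulations are not given. Expected-count Poisson approximations on the Table 2 totals gave anything from about 21% to 99% at RR 1.16, depending mainly on whether a year-by-mode term is fitted. They neither confirm nor refute 80%.

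The two stated figures do roughly agree with each other. With a constant standard error, 80% at RR 1.16 implies a noncentrality of 2.80 × ln(1.18)/ln(1.16) = 2.80 × 1.115 = 3.12 at RR 1.18. That gives power Φ(3.12 − 1.96) = 88%, against the stated figure of over 90%. I therefore take the stated power as correct for the simulated cohort and ask only what a smaller cohort does to it.

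**Share with known mode.** Let m be the share with mode in the GP record (0.55–0.64) and h the share with linked hospital data. If the two are independent, f = m + (1 − m)h.

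- Widest linkage range, h = 0.30 to 0.60: f = 0.55 + 0.45 × 0.30 = 0.685, to f = 0.64 + 0.36 × 0.60 = 0.856.
- Weighted by practice overlap: Data sources gives 37% of THIN and 46% of CPRD practices as unique, so 0.63T = 0.54C, C = 1.167T, and the combined set is T + 0.46C = 1.537T.
  - Keeping the THIN copy of duplicates: h = (0.30 + 0.46 × 1.167 × 0.60)/1.537 = 0.405, and f = 0.55 + 0.45 × 0.405 = 0.732 at the low end.
  - Keeping the CPRD copy: h = (0.37 × 0.30 + 1.167 × 0.60)/1.537 = 0.528, and f = 0.64 + 0.36 × 0.528 = 0.830 at the high end.

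**Effect on power, if 777 389 is before the restriction.** Information scales with f, so power = Φ(δ√f − 1.96). Here δ = 1.96 + 0.84 = 2.80 for 80% power and 1.96 + 1.28 = 3.24 for 90%. The RR detectable with 80% power is exp(ln 1.16/√f).

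| f | Births | Power at RR 1.16 (stated 80%) | Power at RR 1.18 (from 90%) | RR at 80% power |
|---|---|---|---|---|
| 0.685 | 532 511 | 64% | 77% | 1.20 |
| 0.732 | about 569 000 | 67% | 79% | 1.19 |
| 0.830 | about 645 000 | 72% | 84% | 1.18 |
| 0.856 | 665 445 | 74% | 85% | 1.17 |

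Worked line for f = 0.685: √f = 0.828; 2.80 × 0.828 = 2.32; Φ(2.32 − 1.96) = Φ(0.36) = 0.64. The RR 1.18 column starts from exactly 90%; it is a little higher if the article's figure is well above 90%.

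**The case against.** The strongest reply is that the premise rests on silence. The article never says that 777 389 precedes the mode restriction. Every simulated birth carries a mode, which fits an already restricted cohort as well as an unrestricted one. The authors knew the recording rate and cite it from the database that fed the simulation. A journal article also condenses, so a filter may have been applied without being described. Follow-up per birth is shorter in THIN-CPRD (3 007 670/777 389 = 3.87 years) than in HES (34 001 358/8 043 600 = 4.23 years), which suggests that losses not spelled out are already in the primary-care column.

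Part of this stands. A reader might infer that the power was definitely computed on the wrong cohort; the document does not establish that, and the size of the effect has to be conditional. The follow-up gap, however, does not show a mode filter. The THIN inputs were estimated by year group, so loss to follow-up could be in them whatever was done about mode. The CS/VD split does not settle it either, since a simulation can assign a mode to every birth. Nor is this only a detail left out: the article names a planning population, and it is not the eligible one.

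A reader might also infer that only 55–64% of children remain, with power of 55–61% at RR 1.16. That ignores the hospital records which the eligibility rule expressly accepts, so it is not the protocol's plan.

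It is also fair that the study uses all available data, that power sets no recruitment target, and that inference will rest on the observed confidence interval. This limits the consequence to how the study's sensitivity is stated.

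**Conclusion.** The point holds as a mismatch between the described planning population and the eligible one, with a conditional size. As written, the THIN-CPRD simulation is sized on maternal linkage alone, while the analysis also needs a known mode, available for roughly 69–86% of children (73–83% with overlap weighting). If Table 2 is before that restriction, power at RR 1.16 is about 64–74% instead of 80%, power at RR 1.18 is about 77–85% instead of 90%, and the RR detectable with 80% power is about 1.17–1.20. If Table 2 is already restricted, only the description is wrong.

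The range assumes that hospital linkage is independent of GP recording of mode, that practice shares stand for child shares (overlap version only), and that CS share and event rates are the same in children with known mode. The loss would be smaller if linkage were concentrated where GP recording is missing, and larger in the opposite case. None of these values should be adopted as the replacement figure; that has to come from the sponsor's own simulation. The HES power is not affected by this point.

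**What to change.** Base the primary-care simulation on children who are both linked to their mother and have a known delivery mode, from the GP record or a linked hospital record. Replace the THIN-CPRD column of Table 2, and restate the risk ratios detectable with 80% and 90% power in the sample size section and the Abstract from that rerun. If 777 389 already counts only such children, correct the description of the simulation input to say so and leave the power figures unchanged.

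The cost is one rerun of an existing simulation and possibly a slightly less favourable figure, or a single sentence. No new data or design change is needed.

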### Methods

We will compare rates of diagnosis of asthma and other outcomes of interest over time in children born by CS, comparing outcomes according to whether each mother received preincisional antibiotics.

In the primary analysis, we will estimate a probability that each mother received preincisional antibiotics according to year of birth, based on national policy uptake rates in the year of delivery for primary care data. For secondary care data, we will use the response from each hospital indicating the year of local policy implementation.

The major threat to validity in this observational comparison is not from case-mix confounders (indications for and incidence of CS have changed little over the study period); rather they relate to temporal changes in diagnosis and in the recording of outcomes and other exposures which impact on the number of cases identified in routine data. Patterns of diagnosis of childhood asthma, for example, have changed over time, in part driven by the revisions in the national asthma management guideline and the potentially conflicting compliance and prevalence issues faced in meeting specific indicators of the Quality and Outcomes Framework (QOF) introduced in 2004.^29 30^

An analysis reliant on adjustment for confounding factors is unlikely to succeed in controlling for these changes as it is unclear (1) what all the drivers of all these changes have been, (2) whether any covariates exist which accurately describe these changes without substantial missing data and (3) challenges in specification of a functional form for the relationship between these covariates and outcome.

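### Table 2's HES person-years fit a whole year of follow-up in every birth year, not follow-up cut at the end of 2018; stated power is probably somewhat optimistic

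*Protocol article*

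**What the plan says.** All of this is in the Protocol article, section Estimates of sample size and statistical power. Each simulated dataset covers the whole study "with 13 birth cohorts from 2006 to 2018", with "follow-up included across the first 5 years of life (curtailed at the end of 2018".

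Table 2 then gives births and person-years for THIN-CPRD (first figure) and HES (second figure):
- "Total births 777 389 8 043 600"
- "Total person years of follow-up 3 007 670 34 001 358"
- preincision births: "Preincision antibiotics 95 107 954 830"
- preincision person-years: "Preincision antibiotics 290 864 3 136 942"

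The power statements rest on this simulation. Primary care is given 80% power at a 16% relative increase and over 90% at 18%. For the hospital data: "For the HES admission data, we have over 80% power to detect a 10% relative increase in risk of asthma", and 90% at 12%.

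The section does not print births per year, the yearly exposure probabilities that generated the data, or any loss to follow-up. It does not say how the year of birth was counted.

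**The concern.** Births occur throughout the year. With follow-up stopping in December 2018, a child born in 2018 contributes half a year on average, one born in 2017 a year and a half, and so on. The HES person-years look as if each of these cohorts had been given the full calendar year of birth.

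Only cohorts born from 2014 onward lose time through the cut, and these are mostly preincision births. They are the scarce side of the comparison: in primary care Table 2 has 1849 preincision events against 5324 postclamping events. Any excess person-time therefore adds events where they matter most for precision. The primary-care power at RR 1.16 is stated as 80%, so even a small loss takes it below that figure.

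**Working it through.** **Inputs (Table 2)**

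| Row | Births | Person-years | Years per birth |
|---|---|---|---|
| HES total | 8 043 600 | 34 001 358 | 4.227 |
| HES CS | 2 070 500 | 8 661 832 | 4.183 |
| HES VD | 5 973 100 | 25 339 526 | 4.242 |
| HES postclamping | 1 115 670 | 5 524 890 | 4.952 |
| HES preincision | 954 830 | 3 136 942 | 3.285 |
| THIN-CPRD total | 777 389 | 3 007 670 | 3.869 |
| THIN-CPRD postclamping | 111 508 | 501 401 | 4.497 |
| THIN-CPRD preincision | 95 107 | 290 864 | 3.058 |

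**Step 1. Reproduce the HES total.** Assume level annual cohorts.
- Whole birth year credited: 2006-2014 get 5 years, then 4, 3, 2, 1. (9×5 + 10)/13 = 55/13 = 4.231, against 4.227 in the table (0.1% apart).
- Births spread through the year, cut at the end of 2018: 2006-2013 get 5 years, then 4.5, 3.5, 2.5, 1.5, 0.5. (8×5 + 12.5)/13 = 52.5/13 = 4.038. This is a ceiling, because loss to follow-up can only lower it.
- Excess: 4.227/4.038 = 1.047, or 34 001 358 − 8 043 600×52.5/13 = about 1.52 million person-years. By mode: CS 4.183/4.038 = 1.036; VD 4.242/4.038 = 1.050.

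**Step 2. Could unequal cohorts explain it?** Under the end-2018 cut the mean shortfall from 5 years must be 5 − 4.227 = 0.773.
- Straight-line fall by a fraction s from 2006 to 2018: (12.5 − 11.25s)/(13 − 6.5s) = 0.773 gives s = 0.39 for all births. The same equation gives 0.32 for CS and 0.42 for VD.
- Single step: the 2014-2018 cohorts average 2.5 years short, so they hold 0.773/2.5 = 30.9% of births. Per year: (0.309/5)/(0.691/8) = 0.716, or 28% fewer (CS 22% fewer).

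Both assume zero loss. Any loss makes the required fall larger.

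**Step 3. Where the excess falls.** The term in the fitted model (0.2 in 2010 up to 1 in 2014) sums to 7/13 = 54% preincision. Table 2 has 46.0% and 46.1%. Shifting the ramp one year later (0.2 in 2011 up to 1 in 2015) gives 6/13 = 46.2%, so I assume that one. Preincision years per birth with no loss:
- whole birth year: (2.0×5 + 4 + 3 + 2 + 1)/6 = 20/6 = 3.33
- cut at end 2018: (1.2×5 + 0.8×4.5 + 3.5 + 2.5 + 1.5 + 0.5)/6 = 17.6/6 = 2.93

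Adding a constant loss rate fitted to each postclamping row (about 0.3-0.4% a year in HES, 4.2-4.3% in THIN-CPRD):

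| | Table 2 | Whole birth year | Cut at end 2018 | Table / cut |
|---|---|---|---|---|
| HES | 3.285 | 3.31 | 2.92 | 1.126 |
| THIN-CPRD | 3.058 | 3.06 | 2.71 | 1.128 |

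A check for HES that needs no uptake curve: with level CS births, the preincision row can hold at most (4.038 − 0.5388×4.952)/0.4612 = 2.97 years per birth, against 3.285.

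**Step 4. Power.** With the standard error multiplied by k, new power = Φ((1.96 + z)/k − 1.96), where z is 0.842 for 80% and 1.282 for 90%. Poisson information calculations under several readings of the model and of the age pattern gave k of about 1.02 to 1.06.
- k = 1.02: 80% becomes 78.4%; 90% becomes 88.8%.
- k = 1.06: 80% becomes 75.3%; 90% becomes 86.4%.

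These start from the stated power, which I could not reproduce. It implies standard errors of ln 1.16/2.80 = 0.053 (primary care) and ln 1.10/2.80 = 0.034 (HES). Models without a year-by-mode term gave about 0.031 and 0.021; models with it gave at least 0.084 and 0.058.

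**The case against.** The strongest reply is that annual births are not printed, so the table is not impossible. That stands: a steep enough fall in births would give these person-years under the end-2018 cut.

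A reader might close that gap with the statement in the Methods section that "indications for and incidence of CS have changed little over the study period". It does not do so. It belongs to an argument about case-mix and concerns how often and why CS is performed, not how many children are born each year. A fall in births would not contradict it.

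A reader might also infer that both databases are shown to be wrong. The primary-care total of 3.869 is below the 4.04 ceiling, so on its own it shows no excess. The gap between 3.058 and 2.71 depends on primary care having the HES uptake curve. The near-identical preincision shares (46.0% and 46.1%) suggest this but do not prove it. A different curve, rising earlier and levelling off at about 0.86, with a loss of 2.3% a year, can reproduce the primary-care CS rows under the end-2018 cut. It would not explain HES.

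A firm power loss of 3 to 4 points is also tempting. It lies inside the plausible range, but the stated power cannot be rebuilt from what is published, so no exact figure is supported.

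Finally, the study takes all available data, so no sample size depends on this, and 1000 simulations carry a Monte Carlo standard error of about 1.3 points at 80%. Both facts limit the consequence. They do not reconcile the HES person-years with the stated follow-up rule.

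**Conclusion.** The point holds for HES. Its person-years match whole-birth-year credit almost exactly and exceed what follow-up cut at the end of 2018 gives with roughly level cohorts: about 4.7% too high in total and about 12-13% too high in the preincision row. This assumes births spread evenly through the year and no steep fall in births (about 39% in a straight line from 2006 to 2018, or about 28% fewer per year in 2014-2018). The preincision figure also assumes an uptake ramp chosen to fit the tabulated 46% share.

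For primary care, which carries the power claim in the Abstract, the same overstatement is a reasonable inference and not a demonstration. Stated power is probably optimistic by roughly 1 to 5 points. The validity of the planned analysis is not affected.

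**What to change.** Re-run the existing simulation for both databases with half a year of follow-up in the birth year, or with random birth dates, and curtailment on 31 December 2018. Restate the person-years and events in Table 2, and the power figures in the Abstract and in the sample size section. State how the birth year was counted, and print births and the generating exposure probability by year so that the table can be checked. If annual births did fall enough to explain the HES figures, printing them would settle the matter.

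The cost is one re-run of existing code and, probably, slightly less favourable stated power. The design and the data to be collected do not change.
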